### Target Population and Recruitment Strategy

Adults aged 40 and above are the target population. This age group is appropriate for screening for T2D and HT according to the national standard operating procedure for T2D and HT management in primary care [13]. Other recruitment criteria include (1) being usual members of the household, having stayed in the household the night before the interview or not been absent for more than 6 months; (2) being physically and mentally capable of answering the questions; and (3) providing consent to participate in the study.

The starting point of recruitment is a list of all the eligible households in the selected villages (Multimedia Appendix 3). The list will be constructed by a listing team with support of a local authority, listing households in the selected village having at least one adult aged 40 and above. When a household is selected, 1 household member aged 40 and above will be selected for inclusion in the study. If the selected eligible individual is not present in the household during the first-time visit, 2 repeated callbacks and follow-up will be applied. Only if all these attempts fail, the selected participants would be replaced: the respective households would be replaced with the next household in a row of the eligible household list constructed. The replacement household would be selected following the procedure described earlier. If the eligible individuals can be contacted but express refusal to participate in the study after a few times of failed explanation, the individuals as well as the households would be dropped from the study.

### Data Collection Procedure

Data collection process will follow the STEPS survey approach [33], with modification of the sequence of the steps to adapt the data collection to the study context. There are 3 main steps of data collection: (1) structured interviews with questionnaires, (2) anthropometric measurements, and (3) biochemical measurements. The modification will entail data collectors taking anthropometric measurements and biochemical measurements of the eligible individuals before administering the 2 sets of questionnaires.

The anthropometric measurements include measurements of blood pressure, body weight, height, and waist and hip circumferences. For blood pressure measurements, participants will rest at least 15 minutes prior to the measurement and 3 readings will be taken 3 minutes apart from one another, with the left arm recommended for the measurement [33]. For the biochemical measurements, testing of fasting blood glucose (FBG) will be carried out for all the participants (Multimedia Appendix 4) and glycated hemoglobin A_1c_ (HbA_1c_) and creatinine for known participants with T2D or participants having FBG of 126 mg/dl or more (Multimedia Appendix 5). Data will be digitally collected using the KoBoToolbox system developed by the Harvard Humanitarian Initiative [34]*.*

For the point-of-care measurement of FBG (capillary plasma value), the On Call Plus (ACON USA), which is compliant with the US Food and Drug Administration regulations [35], will be used. It is widely used in the WHO PEN program in Cambodia. The HemoCue HbA_1c_ 501 System, whose quality is ensured by the International Federation of Clinical Chemistry and Laboratory Medicine and the National Glycohemoglobin Standardization Program [36], will be employed as a point-of-care test for HbA_1c_. Regarding the anthropometric measurement, Omron JPN500, which is clinically validated by the Association for the Advancement of Medical Instrumentation and European Society of Hypertension [37], will be used to measure blood pressure. A flat weight scale (Seca-803), height measuring system (Seca-217), and ergonomic circumference measuring tape with extra waist-to-hip-ratio calculator (Seca-203) will be used to measure weight, height, and waist and hip circumferences of the participants, respectively. Seca is internationally recognized as producing highly accurate scales equipped with high-precision measuring technology [38].

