## Introduction

Globally, cardiovascular diseases (CVDs) are responsible for the death of 17.9 million people annually, accounting for 31% of all deaths [1]. More than 75% of deaths attributable to CVDs occur in low- and middle-income countries (LMICs), where primary health care (PHC) settings generally do not perform well in the early detection, diagnosis, and monitoring of type 2 diabetes (T2D) and hypertension (HT), which are the leading risk factors for CVDs [1,2]. In regions where early diagnosis and care are not available or inadequate, T2D and HT-related complications—including CVDs, kidney disease, neuropathy, blindness, and lower-extremity amputation—are a significant cause of morbidity and mortality among people with T2D or HT or both [3,4]. The resulting complications will increase health care costs and pose challenges to population health, socioeconomic development, and health systems [5,6], negatively affecting country’s effort to achieve universal health coverage [7]. Globally, adult populations with HT and T2D had increased from 594 million to 1.13 billion between 1975 and 2015 [8] and from 4.7% to 8.5% between 1980 and 2014 (with approximately 422 million living with T2D in 2014), respectively [2]. Access to a lifelong continuum of care is therefore critical for those living with T2D or HT or both as well as for the prevention of CVDs [9]. The World Health Organization Package of Essential Noncommunicable Disease Interventions (WHO PEN) offers substantial international support for PHC services to include care for T2D and HT in LMICs [10].

In Cambodia, CVDs were estimated to account for 24% of the total deaths in 2018 [11], and in 2016 the prevalence rates of T2D and HT were 9.6% and 14.2%, respectively, among adult population between the ages of 18 and 69 years [12]. This seems a significant increase, as the prevalence of T2D between ages 25 and 64 was only 2.9% in 2010 [12]. However, integrated care for T2D and HT in the Cambodian PHC system remains limited [13]. More than two-thirds of the population have never had their blood glucose measured, and more than half of the population with T2D is not receiving treatment [12,14]. The proportion of patients with T2D accessing treatment is low, with few achieving recommended treatment targets [15].

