1. Prevalence of the target population living with T2D	Participants having biochemical measurement of FBG^b^ (capillary plasma value) ≥126 mg/dl (7 mmol/L) and HbA_1c_^c^ level ≥6.5% [24,40,41]	Measurement of FBG Measurement of HbA_1c_
		Have you ever been told by a doctor or other health worker that you have T2D?
	or Participants reporting use of drugs for T2D, irrespective of their biomarker values	
2. Number of the target population with T2D ever tested for T2D	Classified patients with T2D having had FBG tested in the last 3 years	Have you ever had your blood glucose tested in the last 3 years?
3. Number of those tested ever diagnosed for T2D	Tested patients with T2D reporting ever being told by a doctor or other health worker as having T2D	Have you ever been told by a doctor or other health worker that you have T2D?
4. Number of those diagnosed in care	Diagnosed patients with T2D reporting getting treatment/care for their conditions at least once in the past 12 months	Did you get treatment/care for your T2D condition in the past 12 months?
5. Number of those in care receiving treatment	In-care patients with T2D reporting using drugs for T2D or insulin in the past 2 weeks or in-care patients with T2D reporting following advice to lose weight, stop smoking, do physical exercise, and be on special prescribed diet	Are you currently receiving any of the following treatment/advice for your T2D condition prescribed by a doctor or health care worker? Insulin or drugs (medication) that you have taken in the past 2 weeks Are you currently receiving any of the following treatment/advice for your T2D condition prescribed by a doctor or health care worker? Special prescribed diet and advice to lose weight and advice to stop smoking and advice to start or do more physical exercise
6. Number of those receiving treatment being under control	In-treatment patients with T2D having HbA_1c_ level <8% [24]	Measurement of HbA_1c_ for the known T2D

^a^T2D: type 2 diabetes.

^b^FBG: fasting blood glucose.

^c^HbA_1c_: glycated hemoglobin A_1c_.

**Table 3 table3:** Defined groups of participants for each bar of the cascade of care for HT^a^.

Bars of the cascade of care for HT	Definitions	Questions extracted for analysis
1. Prevalence of the target population living with HT	Participants having systolic blood pressure ≥140 mmHg or diastolic blood pressure ≥90 mmHg [12] or	Measurement of blood pressure (mean of the second and third readings)

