	Participants reporting use of drugs for HT, irrespective of their blood pressure values	Have you ever been told by a doctor or other health worker that you have HT?
2. Number of the target population with HT ever tested for HT	Classified patients with HT having had a blood pressure measured in the last 3 years	Have you ever had your blood pressure measured in the last 3 years?
3. Number of those tested ever diagnosed for HT	Tested patients with HT reporting ever being told by a doctor or other health worker as having HT	Have you ever been told by a doctor or other health worker that you have HT?
4. Number of those diagnosed in care	Diagnosed patients with HT reporting getting treatment/care for their conditions at least once in the past 12 months	Did you get treatment/care for your HT condition in the past 12 months?
5. Number of those in care receiving treatment	In-care patients with HT reporting using drugs for HT in the past 2 weeks or	Are you currently receiving any of the following treatment/advice for your HT condition prescribed by a doctor or other health worker? Drugs (medication) that you have taken in the past 2 weeks
	In-care patients with HT reporting following advice to lose weight, stop smoking, do physical exercise, and reduce salt intake	Are you currently receiving any of the following treatment/advice for your HT condition prescribed by a doctor or other health worker? Advice to reduce salt intake and advice to lose weight and advice to stop smoking and advice to start or do more physical exercise
6. Number of those receiving treatment being under control	In-treatment patients with HT having systolic blood pressure <140 mmHg and diastolic blood pressure <90 mmHg [12]	Measurement of blood pressure (mean of the second and third readings) for the known HT

^a^HT: hypertension.

Because of the multistage stratified random cluster sampling, a 3-stage weighting procedure will be applied to account for (1) the fixed number of villages selected in each OD, (2) the fixed number of households selected in each village, and (3) the number of household members aged 40 and above in each selected household [25,30]. The statistic program Stata 14.2 (StataCorp) [42] will be used to perform the quantitative analyses.

Variables used to generate the cascade of care for T2D and HT are shown in Tables 2 and 3, respectively. The explanatory variables are detailed in Multimedia Appendix 6 [43-47].

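### Glucose and blood pressure are measured before the interview, so the survey's own test can be counted as prior testing in bar 2 of both cascades

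*Protocol article*

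**What the plan says.** The Data Collection Procedure section changes the sequence on purpose, giving adaptation to the study context as the reason: "The modification will entail data collectors taking anthropometric measurements and biochemical measurements of the eligible individuals before administering the 2 sets of questionnaires".

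The measurements taken first include both index tests:
- Blood pressure: "The anthropometric measurements include measurements of blood pressure, body weight, height, and waist and hip circumferences".
- Glucose: "testing of fasting blood glucose (FBG) will be carried out for all the participants".

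Tables 2 and 3 in the Statistical Analysis Plan section build bar 2 from one item each:
- T2D: "Have you ever had your blood glucose tested in the last 3 years".
- HT: "Have you ever had your blood pressure measured in the last 3 years".

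Bar 3 requires membership of bar 2 and a yes to "Have you ever been told by a doctor or other health worker that you have T2D" or "Have you ever been told by a doctor or other health worker that you have HT". The denominator is fixed at all participants classified as having the condition. Testing is also listed as an outcome for the bivariate and logistic regression analyses.

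**The concern.** When the bar 2 question is put, every participant has just had a finger-prick and three cuff readings. Nothing in the printed wording tells the respondent to leave these out. A respondent with no earlier test in the window who counts the one just done becomes a false positive for prior testing. Among those without an earlier test, this route produces errors in one direction only.

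At stake is the first leakage point of the cascade. The gap between prevalence and testing would look smaller than it is, and the loss would reappear one step later, as people tested but not diagnosed. A policy reader could then look for the fault in diagnosis when it lies in access to testing. The comparison of care models at bar 2, and the regression with testing as its outcome, use the same misclassified variable.

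**Working it through.** The plan gives no figure for misreported testing, so there is none to reproduce. The sample-size calculation does not enter.

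**Sequence.** Measurement of all participants comes first and the questionnaires second. The bar 2 item has a 3-year window with no end point before the visit. The order and the wording are both printed in the article, and together they leave the route open.

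**Size at bar 2.** Let t be the true share of classified cases tested in the window before the visit, u = 1 − t, and m the share of the untested who count the survey's own test.

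Observed bar 2 = t + (1 − t)·m, so inflation = 100·u·m percentage points.

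| u (assumed) | m (assumed) | Inflation, points |
|---|---|---|
| 0.30 | 0.05 | 100 × 0.30 × 0.05 = 1.5 |
| 0.50 | 0.10 | 100 × 0.50 × 0.10 = 5.0 |
| 0.67 | 0.20 | 100 × 0.67 × 0.20 = 13.4 |

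The upper u is guided by the Introduction: "More than two-thirds of the population have never had their blood glucose measured". That statement covers the general population and testing at any time. Bar 2 concerns people aged 40 and over classified with T2D and a 3-year window, so the true u may be quite different. The article gives no untested share for blood pressure, and no value of m at all. With t = 0.50, a larger m of 0.25 or 0.50 would give an observed bar of 62.5% or 75%.

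In counts, the planning prevalence of 10% applied to the 5072 participants gives about 507 T2D cases. At t = 0.50 and m = 0.10, bar 2 goes from about 254 to about 279, or 25 extra cases.

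**Effect on later bars.** Bar 3 needs both tested and told. An undiagnosed respondent who wrongly says yes at bar 2 still fails bar 3, so bars 3 to 6 do not move. As an illustration, take true bar 2 = 50%, bar 3 = 30%, m = 0.10, and all untested people undiagnosed:
- untested gap: 100 − 50 = 50 points becomes 100 − 55 = 45;
- tested-but-undiagnosed gap: 50 − 30 = 20 points becomes 55 − 30 = 25;
- total not reaching bar 3: 70 points both ways.

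The exception is a diagnosed person with no test in the last 3 years. A false yes would admit that person to bar 3 and possibly beyond.

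**Effect on comparisons.** For two districts with equal m, the observed difference is [t₁ + (1 − t₁)m] − [t₂ + (1 − t₂)m] = (t₁ − t₂)(1 − m). At m = 0.20, a true 30-point difference appears as 30 × 0.80 = 24 points. The order of the districts is kept. If m differs between districts, the observed difference is (t₁ − t₂) + (u₁m₁ − u₂m₂), and the error can go either way.

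**The case against.** The strongest reply is that the decisive evidence is not in view. The tables list only the questions extracted for analysis; the questionnaires are Multimedia Appendices 1 and 2, which are not shown. An instruction to disregard the day's measurements could sit there or in a field manual. This stands: the point is about what the printed plan allows, and one sentence from the sponsor could close it.

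The size is also unknown. It rests on assumed u and m, and the two-thirds figure belongs to a different population. This stands too.

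Two stronger readings are tempting, and the document supports neither.

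- *Everyone will answer yes, so bar 2 is meaningless.* A literal respondent could say yes, but the item reads as a question about testing history and many will take it that way. Nothing in the article puts m near 1.
- *Bar 3 is contaminated as well.* This would need a result, or the call for HbA1c, to be conveyed before the interview as a diagnosis by someone the respondent regards as a health worker. The article states none of this and speaks only of data collectors. HbA1c is also taken in participants already known to have T2D, which suggests that T2D status is established at or before measurement. No counterpart is described for HT. Bar 3 is therefore a conditional risk only.

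Finally, collection ended in mid-October 2020, so reordering cannot help this data set. That is correct and limits the remedy for it. The analysis was still pending when the article was written, however, and the article offers the protocol as a tool for generating cascades and the data as a baseline for monitoring, so the wording matters for later use.

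**Conclusion.** The point holds for bar 2 in both cascades. As printed, measuring first and then asking an unbounded 3-year question can only push the tested bar upward by this route. It understates the untested gap, overstates the tested-but-undiagnosed gap by the same amount among undiagnosed people, and shrinks district differences by (1 − m) when m is equal across districts. It leaves the total undiagnosed gap and bars 3 to 6 intact for undiagnosed respondents.

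The size is 100·u·m points. The illustrative range of 1.5 to 13.4 points depends entirely on assumed u and m and should not be read as an estimate, least of all for HT, where the article gives no untested share. The conclusion also assumes that the unseen questionnaires carry no exclusion of the day's measurements. This is worth correcting, but it does not invalidate the cascade.

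**What to change.** **For the protocol as a tool and for repeat rounds.** Ask the tested and ever-told items for T2D and HT before any measurement, or add *before today's visit* to them, and give results only after the interview. The cost is moving four short questions or adding three words, plus one line of field instruction.

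**For the data already collected.**
1. Check the questionnaires and field instructions for wording that excludes the survey's own measurements. If it exists, state it in the methods; the point is then closed.
2. If it does not, present observed bar 2 as an upper bound with respect to this route, with a sensitivity lower bound that counts undiagnosed respondents as untested. This lower bound equals bar 3 by construction (30% to 55% in the illustration above), so it shows how little the data alone can say about the testing step. It does not correct diagnosed people who wrongly report a test in the last 3 years.
3. State the limitation, and restrict conclusions on the testing gap, on district differences at bar 2 and on the testing regression accordingly.

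The cost is one recoded variable and one sensitivity row per cascade. No sample-size figure changes.

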### Statistical Analysis Plan

For the analysis plan, 6 cascade bars, as explained in Tables 2 and 3, will be used to generate the cascades of care for T2D and HT, respectively. A fixed denominator approach will be followed as it enables readers to see the leakages between stages of the continuum of care [39]. The denominator is the total number of eligible individuals aged 40 and above having T2D (for the T2D cascade of care) and HT (for the HT cascade of care). We will produce the cascade of care for T2D and HT for the selected ODs hosting different existing care models. These cascades of care—in essence, a series of bar charts—will subsequently be translated into cumulative probabilities. The bivariate analysis will be used to identify potential factors associated with the outcome variables—prevalence, testing, diagnosis, in care, in treatment, and under control bars. At the initial stage, the chi-square test will be used to determine the association between explanatory variables and outcome variables. The explanatory variables will include participants’ age, sex, marital status, educational level, household wealth quintile, health care utilization, and care model setting. Variables with statistically significant level (*P*<.2) will be included in a multiple logistic regression model. In addition to the aforementioned variables, BMI, lifestyle, knowledge of T2D and HT, self-management, and social support will be included in the multiple logistic regression model for the outcome variables—in care, in treatment, and under control bars [24,25]. In the multiple logistic regression model, the backward elimination method will be used. The process will start with all the identified explanatory variables. Then, variables with the highest *P* value will be eliminated from the model one by one at a time. The process will be repeated until all the variables in the model are statistically significant with a cut-off point of *P* value <.05. This knowledge will allow us to identify which characteristics stimulate the probability of not reaching the next step in the cascade of care, thereby identifying patient groups not adequately reached.

**Table 2 table2:** Defined groups of participants for each bar of the cascade of care for T2D^a^.

Bars of the cascade of care for T2D	Definitions	Questions extracted for analysis
1. Prevalence of the target population living with T2D	Participants having biochemical measurement of FBG^b^ (capillary plasma value) ≥126 mg/dl (7 mmol/L) and HbA_1c_^c^ level ≥6.5% [24,40,41]	Measurement of FBG Measurement of HbA_1c_
		Have you ever been told by a doctor or other health worker that you have T2D?
	or Participants reporting use of drugs for T2D, irrespective of their biomarker values	
2. Number of the target population with T2D ever tested for T2D	Classified patients with T2D having had FBG tested in the last 3 years	Have you ever had your blood glucose tested in the last 3 years?
3. Number of those tested ever diagnosed for T2D	Tested patients with T2D reporting ever being told by a doctor or other health worker as having T2D	Have you ever been told by a doctor or other health worker that you have T2D?
4. Number of those diagnosed in care	Diagnosed patients with T2D reporting getting treatment/care for their conditions at least once in the past 12 months	Did you get treatment/care for your T2D condition in the past 12 months?
5. Number of those in care receiving treatment	In-care patients with T2D reporting using drugs for T2D or insulin in the past 2 weeks or in-care patients with T2D reporting following advice to lose weight, stop smoking, do physical exercise, and be on special prescribed diet	Are you currently receiving any of the following treatment/advice for your T2D condition prescribed by a doctor or health care worker? Insulin or drugs (medication) that you have taken in the past 2 weeks Are you currently receiving any of the following treatment/advice for your T2D condition prescribed by a doctor or health care worker? Special prescribed diet and advice to lose weight and advice to stop smoking and advice to start or do more physical exercise
6. Number of those receiving treatment being under control	In-treatment patients with T2D having HbA_1c_ level <8% [24]	Measurement of HbA_1c_ for the known T2D

^a^T2D: type 2 diabetes.

^b^FBG: fasting blood glucose.

^c^HbA_1c_: glycated hemoglobin A_1c_.

**Table 3 table3:** Defined groups of participants for each bar of the cascade of care for HT^a^.

Bars of the cascade of care for HT	Definitions	Questions extracted for analysis
1. Prevalence of the target population living with HT	Participants having systolic blood pressure ≥140 mmHg or diastolic blood pressure ≥90 mmHg [12] or	Measurement of blood pressure (mean of the second and third readings)
	Participants reporting use of drugs for HT, irrespective of their blood pressure values	Have you ever been told by a doctor or other health worker that you have HT?
2. Number of the target population with HT ever tested for HT	Classified patients with HT having had a blood pressure measured in the last 3 years	Have you ever had your blood pressure measured in the last 3 years?
3. Number of those tested ever diagnosed for HT	Tested patients with HT reporting ever being told by a doctor or other health worker as having HT	Have you ever been told by a doctor or other health worker that you have HT?
4. Number of those diagnosed in care	Diagnosed patients with HT reporting getting treatment/care for their conditions at least once in the past 12 months	Did you get treatment/care for your HT condition in the past 12 months?
5. Number of those in care receiving treatment	In-care patients with HT reporting using drugs for HT in the past 2 weeks or	Are you currently receiving any of the following treatment/advice for your HT condition prescribed by a doctor or other health worker? Drugs (medication) that you have taken in the past 2 weeks
	In-care patients with HT reporting following advice to lose weight, stop smoking, do physical exercise, and reduce salt intake	Are you currently receiving any of the following treatment/advice for your HT condition prescribed by a doctor or other health worker? Advice to reduce salt intake and advice to lose weight and advice to stop smoking and advice to start or do more physical exercise
6. Number of those receiving treatment being under control	In-treatment patients with HT having systolic blood pressure <140 mmHg and diastolic blood pressure <90 mmHg [12]	Measurement of blood pressure (mean of the second and third readings) for the known HT

^a^HT: hypertension.

Because of the multistage stratified random cluster sampling, a 3-stage weighting procedure will be applied to account for (1) the fixed number of villages selected in each OD, (2) the fixed number of households selected in each village, and (3) the number of household members aged 40 and above in each selected household [25,30]. The statistic program Stata 14.2 (StataCorp) [42] will be used to perform the quantitative analyses.

Variables used to generate the cascade of care for T2D and HT are shown in Tables 2 and 3, respectively. The explanatory variables are detailed in Multimedia Appendix 6 [43-47].

The population in the catchment areas is not confined to seek care only in the designated public health facility. To address this, we will also collect patient registry data from the public health facilities in the study setting with regard to patients receiving treatment for triangulating the care model selected.

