Inspired by noticeable successes in providing the continuum of care to people living with HIV in Cambodia [22], we adapted the HIV test-treat-retain cascade of care [23] in this study protocol to assess the continuum of care for patients living with T2D or HT or both. This method documents how many patients are lost to follow-up between the stages of testing and diagnosis, linkage with and retention in care, and adherence to treatment and control of health conditions. The cascade-of-care approach outlines the aforementioned sequential steps in long-term care. Recently, this approach has been applied to T2D and HT by pooling secondary data from cross-sectional studies of nationally representative surveys in LMICs [24,25]. This was used to produce cascades of care as an approach to assess the performance of health systems to meet the continuum of care for patients living with T2D or HT or both. Two studies, one in the United States and the other in South Africa, developed and field tested the cascade of care for T2D and HT [26,27]. Their analysis was mainly based on extracted secondary data from broader nationally representative surveys, not specifically designed for this purpose.

Given that Cambodia implements T2D and HT services through 3 different care models, we propose the cascade-of-care approach to assess the performance of these care models along the continuum of care. We will do so using primary data collection. This study protocol aims to serve as a tool to generate the cascades of care for T2D and HT for the 3 care models using the primary data of a population-based survey. The specific aims are as follows:

To generate the cascades of care for T2D for (1) hospital-based care, (2) health center–based care (WHO PEN), (3) community-based care (Peer Educator Network), and (4) coexistence of 1, 2, and 3;To generate the cascades of care for HT for (1) hospital-based care, (2) health center–based care (WHO PEN), (3) community-based care (Peer Educator Network), and (4) coexistence of 1, 2, and 3;To compare the cascades of care for T2D between the care models 1-4;To compare the cascades of care for HT between the care models 1-4.

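### Aims 3-4 compare care models through district bars with no stated case-mix adjustment, and the only adjusted model may drop care model and is not linked back to the cascade

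*Protocol article*

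**What the plan says.** The specific aims at the end of the Introduction include "To compare the cascades of care for T2D between the care models 1-4", with a matching aim for HT.

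The Statistical Analysis Plan section then sets out two strands.

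- **The bars.** "We will produce the cascade of care for T2D and HT for the selected ODs hosting different existing care models". The denominator is all classified cases: "A fixed denominator approach will be followed as it enables readers to see the leakages between stages of the continuum of care". The bars "will subsequently be translated into cumulative probabilities". Later in the section, a three-stage weighting is described. It accounts for the fixed number of villages per OD, the fixed number of households per village and the number of members aged 40 and above in the household.
- **The regression.** Candidate variables are age, sex, marital status, educational level, "household wealth quintile, health care utilization, and care model setting". Those with P<.2 in bivariate tests "will be included in a multiple logistic regression model", and further variables are added for the last three bars. Backward elimination follows: "The process will be repeated until all the variables in the model are statistically significant with a cut-off point of *P* value <.05". The stated purpose is to "identify which characteristics stimulate the probability of not reaching the next step in the cascade of care".

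Under Study Design, five of 103 ODs are selected purposively. Table 1 gives one OD to each care model, except health center-based care, which has two.

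**The concern.** A comparison of cascades is a comparison of bar heights. The five ODs lie in different provinces, and their T2D and HT cases may differ in age, sex, education and wealth. Selection weights make each OD's bar represent that OD; they do not give the ODs a common mix. The Discussion relies on random selection within ODs for internal validity, but this does not balance one OD against another.

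The regression could supply an adjusted contrast, since care model setting is a candidate. It is designed for another question, however, and P-value selection decides whether that term and the case-mix terms survive. A care-model contrast could be present for one bar and absent for the next, or be adjusted for different things along the same cascade. At stake is whether a gap between two cascades is read as a difference in care-model performance when part of it is who the patients are.

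**Working it through.** **1. The plan's own figures.** The printed formula gives 1.96² × 0.1 × 0.9 × 1.5 × 1.2 / (0.24 × 4.6 × 0.01²) = 5637.1, matching the stated 5637. The planned sample is 24 × 44 × 5 = 5280, also as stated. These figures do not test the present point, but they give the case numbers used below.

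**2. Expected T2D cases per OD**, at the protocol's 10% prevalence and an equal split:
- planned: 5280 / 5 × 0.10 = 105.6
- with the 5072 who took part: 5072 / 5 × 0.10 = 101.4

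**3. Case-mix shift with no care-model effect.** With two covariate groups, crude shift = (difference in group share between ODs) × (difference in bar between groups). The article gives neither input, so both are assumed.

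| Share difference | Bar difference between groups | Crude shift |
|---|---|---|
| 5 points | 20 points | 1 point |
| 15 points | 20 points | 3 points |
| 20 points | 20 points | 4 points |
| 40 points (30% v 70%) | 40 points (30% v 70%) | 16 points |

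The last row is an extreme mix, shown only to mark the range.

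**4. Sampling error for comparison.** For a T2D bar near 50%, using the protocol's design effect of 1.5, the 95% half-width for a difference between two ODs is 1.96 × √(2 × 1.5 × 0.5 × 0.5 / 105.6) = 0.165, or 16.5 points. For a bar near 30% it is 15.1 points. Shifts of 1 to 4 points lie well inside this. The article says HT is more prevalent, so HT has more cases and smaller sampling error; a shift does not shrink with sample size.

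**5. Why the scale needs stating.** An odds ratio of 2 corresponds to different gains at different baseline bars:

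| Baseline bar | Bar at OR 2 | Difference |
|---|---|---|
| 10% | 18.2% | 8.2 points |
| 30% | 46.2% | 16.2 points |
| 50% | 66.7% | 16.7 points |
| 70% | 82.4% | 12.4 points |
| 90% | 94.7% | 4.7 points |

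A logistic coefficient alone therefore does not give a bar height or a gap in points.

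**6. The same kind of model can give standardised bars.** Take group-specific bars of 30% and 70% in OD A, a conditional odds ratio of 2 for OD B (giving 46.2% and 82.4%), and upper-group shares of 30% in A and 70% in B (all assumed).
- Crude: A = 0.7 × 0.30 + 0.3 × 0.70 = 42.0%; B = 0.3 × 0.462 + 0.7 × 0.824 = 71.5%. Difference 29.5 points.
- Standardised to a 50/50 mix: A = 50.0%; B = 64.3%. Difference 14.3 points.

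**The case against.** The case on the other side has several parts.

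- **Crude bars are a proper target.** Aims 1-2 generate each OD's cascade to show leakage and unmet need in the actual population. This stands, and the crude bars should be kept. It does not settle aims 3-4.
- **Adjustment is planned in part.** Care model setting and the demographic covariates are candidates for the model of each bar. This stands too. The weakness is that P-value selection can remove either, so the contrast is not guaranteed.
- **The choice of effect measure is detail that an article may leave out.** This is fair as far as it goes. A reader might infer that the adjusted results will be odds ratios only, or that they cannot be placed on the cascade. The documents support neither: no effect measure is named, and step 6 shows that such a model yields standardised bars. A reader might also fear that odds ratios will be ranked across bars, but no such ranking is planned. What remains is that the article fixes the bars, the model, its purpose and the elimination rule, and none of these serves the comparison in aims 3-4.
- **The effect may be small.** For T2D, the modest assumed shifts are lost in sampling error. This stands, and it limits how much the point can claim.
- **Standardising does not isolate the care model.** Care model remains confounded with district. This stands and must be stated with the results.

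**Conclusion.** The concern holds in a limited form. The comparison of cascades is stated through OD bars without case-mix adjustment, and the weights do not supply it. The one adjusted analysis is aimed at patient characteristics, may lose the care-model or case-mix terms bar by bar, and has no stated route back to percentages.

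The article does not allow the bias to be computed. The 1 to 4 point shifts are illustrations from assumed inputs and, for T2D, fall within a half-width of about 16.5 points; that figure assumes 10% prevalence, an equal split across ODs, a design effect of 1.5 and a bar near 50%. It would be wrong to conclude that the crude comparison is known to mislead. The supported conclusion is that a better-matched analysis for aims 3-4 is available from the planned data and software and should be specified.

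**What to change.** For aims 3-4, fit for each bar a survey-weighted logistic model that always keeps care model setting, age, sex, marital status, education and wealth, with no P-value selection. Leave out health care utilization, knowledge and self-management, because they may lie on the pathway from care model to outcome. Use marginal standardisation (predictive margins) to obtain each OD's bar at a common case-mix, show these beside the crude bars, and report adjusted differences in percentage points with 95% CI.

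Keep the crude bars for aims 1-2. Odds ratios may be kept for the analysis of patient characteristics.

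State alongside the results that standardisation removes measured individual case-mix only: with one OD per care model, and two for health center-based care, care model remains confounded with district.

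The cost is one post-estimation step per model in the planned Stata and one more panel per figure, with no new data. The drawbacks are two sets of bars to explain and less stable T2D estimates with about 100 cases per OD, most of all for the under-control bar.
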